### Measures

All study measures are presented in Table 1.

#### Baseline

*Socio-demographic* characteristics (e.g., gender, ethnicity, height, weight, education, employment).*Illness-history/clinical* characteristics (e.g., diagnostic type, previous episodes, history of psychosis).*Service use* (e.g., past/current pharmacological & non-pharmacological treatments, hospitalisations).

#### Primary outcome

*Psychosocial functioning*: The FAST [43] will be used to assess levels of functioning. The FAST consists of 24 items (rated on 0-3 scale), which assess 6 areas of daily life functioning: autonomy (ability to doing this alone and making own decisions); occupational functioning (ability to work); cognitive functioning (patient’s cognitive abilities); financial issues (ability to manage finances); interpersonal relationships (social relationships with family and friends); and leisure time (engaging in hobbies and physical activity). Higher scores indicate greater difficulties. The FAST was specifically designed to examine difficulties experienced in BD and is recommended for clinical research by the ISBD [34].

#### Secondary outcomes

*Cognition*: Composite score and individual domain scores for attention and processing speed (Digit-symbol Coding test from the Wechsler Adult Intelligence Scale 4th edition [44]; Trail Making Test A [TMT] [45]), working memory (Digit Span test from the Wechsler Adult Intelligence Scale 4th edition) [44], verbal learning and memory (Verbal Paired Associates) [46], and executive functioning (Hotel Test [47]; FAS letter fluency test [48]; TMT B [45]). The global cognition composite score will be calculated as per [31].*Mood symptoms* using HAMD [49] for depression and YMRS [50] for hypomania/mania.*Subjective cognitive complaints* using the Perceived Deficits Questionnaire – Depression (PDQ-D) [51].Attainment of patient-defined goals using the Goal Attainment Scaling (GAS) [52].*Sleep quality* the using Pittsburgh Sleep Quality Index (PSQI) [53].*Health related quality of life* using Euro Quality of Life – 5 Dimension – 3 Levels (EQ-5D-3L) [54].

#### Mechanistic outcomes

*Global cognition* using a composite score of individual cognitive tests*.**Saliva samples* to estimate Cortisol Awakening Response (CAR), full-day cortisol secretion levels, and the ratio of cortisol to DHEA [36, 55]*Metacognition* using the Metacognitive Awareness Inventory (MAI) [56] and the Torres’ ratings for metacognitive knowledge/experience [57].Positive and negative *affect fluctuation* using the Positive and Negative Affect Schedule – Short Form (PANAS-SF) [58].

Saliva samples will be self-collected by participants on one day within the three days following the assessment at W0 and W13. Six samples will be collected over the day using the cotton swab method: 0, 15, 30, 45, and 60 min after awakening, and then at 8pm [59]. Self-collection packs containing saliva tubes will be sent back to the London site, using Royal Mail Tracked delivery.

PANAS will be completed by participants twice daily for seven consecutive days following the assessment at W0 and W13, using a secure web platform (Qualtrics; https://www.qualtrics.com/). Variability between daily mood ratings throughout the week will subsequently be computed to measure daily affect fluctuation, split into positive and negative volatility (the measure of interest; defined as the change in the mean of the mood ratings between ratings) and positive and negative noise (defined as variability in affect that does not persist between ratings) [60]. Participants will be prompted to complete these ratings with automated email reminders.

#### Tertiary outcomes

Pre-randomisation variables: *Premorbid IQ* using the Test of Premorbid Functioning (TOPF) [61]; *childhood trauma* using the Childhood Trauma Questionnaire – Short Form (CTQ-SF) [62]; *anxiety* using the Hamilton Rating Scale for Anxiety (HAMA) [63]; *chronotype* using the Morningness-Eveningness Questionnaire (MEQ) [64]; and *traits of borderline personality disorder* using the MacLean Screening Instrument for Borderline Personality Disorder (MSI-BPD) [65].Therapy-related variables: *Session attendance* using the individual therapy log for each participant; *treatment adherence* using the pre-defined threshold of ≥ 20 therapy hours; and *therapeutic alliance* for both the therapist and the client using the Working Alliance Inventory-Short Revised (WAI-SR) [66].

#### Other measures

At screening and baseline, participants will undergo a diagnostic interview for common mental disorders (i.e., major depressive episode, manic and hypomanic episode, alcohol use disorder, substance use disorder) using the MINI 7 [67], whilst suicidality will be assessed using MINI 5 [67]. A brief screening for indications of cognitive decline associated with organic/neurological condition will be also conducted using the Montreal Cognitive Assessment – Telephone version (MoCA-T) [68]. Participants in the intervention group will also complete a CR satisfaction questionnaire [69]. Finally, all participants will be asked to complete brief mood assessments on a weekly basis from W1 to W24 using the Maudsley Visual Analogue Scale (MVAS) which will be only used to monitor mood and wellbeing of participants during the trial [70].

### Statistics

We provide a brief summary here, however a detailed statistical analysis plan (SAP) will be developed by the trial statisticians and approved by the trial team and the oversight committees. The main analysis will adopt the intention-to-treat principle and will be conducted after data collection has been completed, the data cleaned, and the database locked.

To ascertain the differences in primary and secondary outcome measures between participants randomised to CR + TAU and TAU alone, mean differences between the groups (and their 95% confidence intervals) in the primary (FAST score at W25) and secondary outcomes will be estimated using mixed-effects linear regression models with the W13 and W25 measures of the outcome in question as dependent variables. Models will include a random intercept for participants, time, and time-by-treatment terms (to allow for extraction of mean differences between treatment groups at different time points), baseline measure of the outcome and site as pre-specified covariates. Standardised effect sizes will be computed, by dividing the estimated group difference by the pooled baseline standard deviation of the measure, to quantify the effect of treatment on primary and secondary outcomes. We will assess whether baseline characteristics are predictive of missing data and include these in the analysis models using maximum likelihood methods under the missing-at-random assumption to account for missing data.

Treatment effect mediation via mechanistic measures will be assessed either using structural equation modelling or causal mediation analysis (e.g., *paramed* command in Stata), adjusting for baseline measures of the mediator and outcome, site, age, gender, and other potential mediator-outcome confounders [71]. We will use the W13 measures of the putative mediator variables and W25 measure of the outcome in mediation models. We will explore whether treatment effects on the global cognition measure are mediated via cortisol measures and whether treatment effects on the FAST are mediated via global cognition, metacognition, and/or PANAS affect fluctuation.

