## Methods

### Trial design

This is a two-arm parallel group, assessor-blind, randomised controlled trial (RCT) comprising a 12-week intervention period followed by a 12-week follow-up period. Assessments will be conducted at week 0 (W0; baseline) and then at week 13 (W13; post) and 25 (W25; follow-up) post-randomisation. Two hundred and fifty participants (*N* = 250) will be randomised in a 1:1 ratio to either CR plus TAU (*n* = 125) or TAU alone (*n* = 125). See Fig. 1 for the study flowchart.

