### Intervention

Participants in the treatment arm will receive a 12-week course of CR therapy using the online software CIRCuiTS™ (www.circuitstherapy.com). CIRCuiTS™ is a manualised CR approach, developed according to the key principles of CR (e.g., errorless learning, scaffolding, positive feedback, strategy development) [41]. CIRCuiTS™ employs rigorous cognitive training with computerised tasks, emphasises the identification and implementation of useful strategies, supports the development of metacognitive skills, as well as the transfer of cognitive skills and strategies to daily life activities.

CR will be delivered to participants over the 12-week intervention period. Sessions are one-on-one 1-h with the therapist, either in person or remotely (i.e., video call). Additionally, all participants in therapy have access to CIRCuiTS™ for independent sessions, with practice tasks agreed with the therapist. The target for therapy engagement is 2–3 hourly sessions per week aiming at a total of 30–40 sessions over 12 weeks.

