### Sample size and power

Our sample size estimation was based on the CRIB study findings: a standardised effect size of 0.49 on the Functional Assessment Short Test (FAST) at W25, a correlation of 0.7 between baseline and follow-up, and an intraclass correlation coefficient (ICC) of 0.02 [31]. Accounting for the effect of therapist clustering, precision gain from one pre and two post-randomisation repeated measures, and an attrition rate of 15%, a power calculation suggested that including 125 participants per arm gives 90% power to detect an effect size of 0.37, which is smaller than the CRIB study reported effect size (i.e., it is a conservative estimation, due to a propensity for small samples to overestimate treatment effects).

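### The sample size allows for therapist clustering (ICC 0.02), but the stated primary model has no therapist term; if therapists differ as planned for, the W25 interval would be too narrow

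*Protocol article*

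**What the plan says.** Under Sample size and power, the protocol article takes its planning values from the pilot trial: "a correlation of 0.7 between baseline and follow-up" and "an intraclass correlation coefficient (ICC) of 0.02". The calculation is described as "Accounting for the effect of therapist clustering, precision gain from one pre and two post-randomisation repeated measures, and an attrition rate of 15" per cent, and it concludes that "including 125 participants per arm gives 90% power to detect an effect size of 0.37".

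Under Statistics, the primary and secondary outcomes are to be analysed by mixed-effects linear regression on the W13 and W25 values. "Models will include a random intercept for participants, time, and time-by-treatment terms", with the baseline value of the outcome and site as pre-specified covariates. Baseline characteristics that predict missingness are to be added. The section names no therapist random effect, partially nested structure or cluster-robust variance, and neither does any other section. It describes itself as a brief summary, with a detailed SAP to follow.

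CR is delivered one-on-one by therapists (Intervention). The TAU arm is offered a therapist session only after the W25 assessment (Treatment adherence and retention).

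**The concern.** The design treats outcomes of CR participants who share a therapist as correlated; the stated analysis treats them as independent. The participant intercept handles repeated measures within a person, not likeness between people. The site covariate is common to both arms, so it cannot take up a component present only under CR. If that component is real, the standard error of the CR minus TAU difference is understated, always in the direction that favours declaring an effect. At stake are the confidence interval and p-value for FAST at W25. The sample size has already been increased to allow for this variance component.

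**Working it through.** **Inputs from the article.** 125 per arm, 15% attrition, correlation 0.7, ICC 0.02, effect 0.37, power 90%. Analysed per arm: n = 125 × 0.85 = 106.25. Residual variance after baseline adjustment, in SD² units: 1 − 0.7² = 0.51.

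**Assumptions.** Two-sided 5% level (the article gives 95% intervals but no alpha). Clustering in the CR arm only, one therapist per participant and equal caseloads. Number of therapists k = 12, 8 or 4; the last is one per site. The scale of the ICC is not stated, so both readings are shown.

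**The plan's own figure.** Ignoring clustering, the variance of the difference is 2 × 0.51/106.25 = 0.0096 (SE 0.0980), and power at 0.37 is 96.5%. With design effect DE = 1 + (m − 1) × 0.02 in both arms, power is 91.6% at m = 15 patients per therapist, 90.4% at m = 18 and 89.5% at m = 20. With DE in the CR arm only it is 90.2% at m = 36. Caseload is not stated, so 90% cannot be reproduced uniquely. It is compatible with the inputs and is not shown to be wrong.

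**True SE against model SE.**
- ICC as a share of residual variance: m = 106.25/k, SE ratio = √((1 + DE)/2).
- ICC as a share of total variance: true variance = 0.0096 + 0.02/k, SE ratio = √(true variance/0.0096).
- Actual two-sided error = 2Φ(−1.96/SE ratio).

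| Therapists | Residual scale: DE | SE ratio | Error | Total scale: variance | SE ratio | Error |
|---|---|---|---|---|---|---|
| 12 | 1.157 | 1.039 | 5.9% | 0.01127 | 1.083 | 7.0% |
| 8 | 1.246 | 1.060 | 6.4% | 0.01210 | 1.123 | 8.1% |
| 4 | 1.511 | 1.121 | 8.0% | 0.01460 | 1.233 | 11.2% |

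The interval is too narrow by 1 − 1/ratio: about 4% to 11% on the residual scale and 8% to 19% on the total scale.

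**Check by simulation.** 20,000 runs per scenario of a W25 analysis of covariance with site fixed effects, 106 per arm, and therapists nested in four sites in the CR arm only. This is a simplification of the two-visit model. For 12, 8 and 4 therapists, the error was 6.0%, 6.8% and 8.1% (residual scale) and 6.9%, 8.3% and 11.2% (total scale). With no therapist variance it was 4.9% to 5.4%. The excess therefore comes from the omitted term, and the site covariate does not remove it.

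**Effect of adding the term.** Satterthwaite df = V²/(V₁²/(k − 1) + V₀²/(n − 1)). V₀ = 0.51/106.25 = 0.0048 is the TAU variance, V₁ is the CR variance including therapist, and V = V₀ + V₁. Widening = (t quantile/1.96) × SE ratio − 1. Power is at 0.37, from the noncentral t.

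| Therapists | Residual scale: df | Wider by | Power | Total scale: df | Wider by | Power |
|---|---|---|---|---|---|---|
| 12 | 35.5 | 8% | 94% | 31.6 | 13% | 92% |
| 8 | 21.8 | 12% | 93% | 18.7 | 20% | 89% |
| 4 | 8.2 | 31% | 84% | 6.6 | 51% | 74% |

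**The case against.** The strongest reply is that the Statistics section is a declared summary, that the SAP is not shown, and that the sample-size text proves the team knows about therapist clustering. Nothing says the list of terms is complete. This stands in part: the SAP may well contain the term. But the section does more than leave the matter open. It names the method, the random effect, the fixed terms and the pre-specified covariates, and that structure conflicts with the article's own design assumption. The conflict needs reconciling wherever the term ends up.

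A reader might infer that the trial's type I error does exceed 5%. The documents do not support that. It would require real therapist variance in this trial and a SAP that adds no term. The number of therapists, the caseload and the scale of the ICC are all unstated, and the 11% figure needs both four therapists and the total-variance reading.

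A reader might also infer that the remedy costs almost nothing because the sample size allows for clustering. That holds with many therapists, when the inflation is also small. With four therapists, where the inflation is largest, the honest interval is much wider and power falls below 90%.

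Nor do the documents show that every secondary result is affected, because the ICC is given alongside the FAST inputs only. They do not say that therapy logs record therapist identity, nor that each participant keeps one therapist.

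**Conclusion.** The point holds conditionally: the stated model omits a variance component that the sample size relies on. If therapists differ to the degree the planning ICC implies and the model is fitted as written, two-sided error for FAST at W25 would be about 6% to 8% (ICC on residual variance) or about 7% to 11% (on total variance) for 12 down to 4 therapists. With more therapists the excess shrinks; with no therapist variance there is none. The direction is firm, but the size rests on figures the article does not give. The stated 90% power is not shown to be wrong. This should be fixed, but it is not a demonstrated error in the trial's conclusions.

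**What to change.** Before database lock:

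- Add a therapist random effect in the CR arm only (a partially nested model) to the primary model and, for consistency, to the secondary models.
- Use Satterthwaite or Kenward-Roger degrees of freedom, since therapists are likely to be few.
- Confirm that therapist identity is in the analysis dataset, and state how participants who change therapist are assigned.
- Report the number of therapists, their caseloads and the estimated therapist ICC.
- If the SAP already has the term, align the published description with it. If it is left out deliberately, explain why clustering is assumed for the sample size but not modelled.

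The cost is one model term and a data check; recruitment need not change on this account with 8 or more therapists. Intervals widen by roughly 8% to 20% with 12 to 8 therapists, and power at 0.37 stays at about 89% or more. With only four therapists they widen by about 31% to 51% and power is about 74% to 84%, so the stated 90% should then be restated. Making the change after unblinding would look data-driven.

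### With ordinary residuals, the random-intercept model pools the W13 and W25 variances, so the W25 standard error is miscalibrated if those variances differ

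*Protocol article*

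**What the plan says.** The Statistics section of the protocol article describes one model for the primary and secondary outcomes: "mixed-effects linear regression models with the W13 and W25 measures of the outcome in question as dependent variables". On its terms it says: "Models will include a random intercept for participants, time, and time-by-treatment terms". The fixed covariates are "baseline measure of the outcome and site as pre-specified covariates". Missing outcomes are handled by "maximum likelihood methods under the missing-at-random assumption to account for missing data".

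Treatment is allowed to interact with time, but no interaction of baseline with time is listed. The section does not state a residual covariance structure or the type of standard error. It also describes itself as a summary: "We provide a brief summary here, however a detailed statistical analysis plan (SAP) will be developed".

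The primary endpoint is FAST at W25 alone. The only correlation given, under Sample size and power, is "a correlation of 0.7 between baseline and follow-up". It is not broken down by visit, and no SD by visit appears anywhere.

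**The concern.** A random intercept over two visits, combined with independent residuals of constant variance, is compound symmetry: one variance for both visits. The primary estimand concerns only the second visit, yet its standard error would be built from both. If FAST, after baseline adjustment, is more variable at W25 than at W13, the primary confidence interval is too narrow and the type I error exceeds its nominal level. If it is less variable, the interval is too wide and power is lost. The W13 intervals err in the opposite direction.

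Unequal spread is plausible here. Participants enter euthymic, W13 falls just after therapy ends, and W25 follows 12 weeks without therapy. The same model serves HAMD and YMRS, both of which are restricted at entry to scores below 8.

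**Working it through.** **Inputs from the article.** 125 per arm, 1:1; 15% attrition; baseline-to-follow-up correlation 0.7; ICC 0.02; 90% power for an effect of 0.37. Completers: 125 × 0.85 = 106.25 per arm, about 212 in all. Alpha is not stated; two-sided 5% is assumed, in line with the 95% intervals.

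**The plan's own figure.** Baseline adjustment at a single visit leaves a variance factor of 1 − 0.7² = 0.51. With 106.25 per arm and an effect of 0.37, power is 96.5% before clustering. A design effect of 1 + (m − 1) × 0.02 in both arms gives 91.6% at m = 15 and 89.1% at m = 21. Applied to the CR arm only, it gives 91.4% at m = 30 and 89.3% at m = 40. So 90% is attainable, but the number of participants per therapist is not stated and the figure cannot be reproduced exactly. It does not bear on k.

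**Standard error at W25.** Let V13 and V25 be the residual variances after baseline adjustment, and k = √(V25/V13). With complete data and n per arm:

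- true variance of the W25 contrast: 2·V25/n
- variance reported under compound symmetry: 2·[(V13 + V25)/2]/n
- reported SE / true SE = √[(V13 + V25)/(2·V25)] = √[(1 + 1/k²)/2]

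The sample size cancels. The actual two-sided error is 2·[1 − Φ(1.96 × ratio)]. For k = 1.2: 1/1.44 = 0.694; (1 + 0.694)/2 = 0.847; the square root is 0.920; 1.96 × 0.920 = 1.80, which gives 7.1%.

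| k (assumed) | SE ratio | Type I error |
|---|---|---|
| 0.9 | 1.057 | 3.8% |
| 1.0 | 1.000 | 5.0% |
| 1.1 | 0.956 | 6.1% |
| 1.2 | 0.920 | 7.1% |
| 1.3 | 0.892 | 8.0% |

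At W13 the ratio is √[(1 + k²)/2]. At k = 1.2 this is √1.22 = 1.10, a standard error about 10% too large.

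**Check by simulation with missing data.** REML fits, 250 participants, 1,500 runs per scenario, 10% missing at W13 and 15% at W25 completely at random, and an assumed residual correlation of 0.4 between visits. Monte Carlo error near 5% is √(0.05 × 0.95/1500), about 0.6 points. The alternative model has an unstructured covariance and a separate baseline slope at each visit.

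| k | Random intercept: SE ratio, type I error | Alternative: SE ratio, type I error |
|---|---|---|
| 0.85 | 1.083, 3.7% | 0.989, 5.6% |
| 1.0 | 1.019, 4.9% | 1.021, 5.0% |
| 1.1 | 0.947, 6.5% | 0.992, 4.9% |
| 1.2 | 0.891, 7.3% | 0.968, 5.4% |
| 1.3 | 0.871, 9.0% | 0.982, 5.7% |

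The largest absolute bias in any scenario was 0.004 SD.

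**Does the single baseline slope matter by itself?** Holding k = 1 and letting the true slopes be 0.8 and 0.7, the single-slope model had an SE ratio of 1.00 and type I error of 5.5%. With slopes 0.75 and 0.6 it had 1.03 and 4.3%. Both are within, or close to, simulation noise.

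A baseline correlation that falls over time matters only if it makes the residual variances unequal. With equal total SDs and correlations of 0.8 and 0.7, V13 = 1 − 0.64 = 0.36 and V25 = 0.51. Then k = √(0.51/0.36) = 1.19 and the SE ratio is √(0.435/0.51) = 0.92. This is the same mechanism as above, not a second one.

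**The case against.** The strongest reply is that residual structure and standard-error type are details a protocol article leaves to the SAP, and the section says it is only a summary. This stands in part. A reader might infer that the model compels equal variances at the two visits. The text does not say so, because a random intercept can be combined with visit-specific residual variances or robust standard errors without contradicting any of it. What remains is that the random intercept is the only covariance feature named, and an SAP that carries it over with software defaults would inherit the problem.

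A reader might also infer that the standard error is wrong whenever the visits differ in any respect. The calculations do not support that: only unequal residual variances matter, and a slope difference alone is nearly harmless.

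Nor does the article support the inference that the primary interval is too narrow. It gives one correlation and no SD by visit, so both size and direction are assumed. The euthymia argument does not clearly separate the visits. W13 is already three months after entry, by which time spread may have widened, and withdrawal for symptom exacerbation could trim extreme late scores. Large ratios are easier to imagine for the mood scales, which are secondary, than for FAST.

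**Conclusion.** The point holds as a conditional one. If the stated model is fitted with homoscedastic residuals, the W25 standard error pools the W13 and W25 residual variances and is miscalibrated to the extent that they differ. A 10% difference in residual SD moves the standard error by about 4% to 6% (type I error 6.1% at k = 1.1, 3.8% at k = 0.9). At k = 1.2 the standard error is about 8% too small and type I error about 7.1%. At k = 1 nothing changes. The treatment estimate is unbiased in all the scenarios examined.

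These figures rest on assumed values of k, on a two-sided 5% level, and, in the closed form, on complete data. The article does not show that the primary analysis is wrong. The case for changing it is that the better specification is calibrated in either direction at almost no cost.

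**What to change.** In the SAP, before unblinding, fit the W13 and W25 outcomes with an unstructured 2x2 residual covariance in place of the random intercept, or keep the random intercept and allow a separate residual variance at each visit. Add a baseline-by-time term. Keep time, time-by-treatment and site as they are, and apply the same specification to the secondary outcomes.

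The cost is about two parameters: compound symmetry has two covariance parameters and the unstructured form three, and baseline-by-time adds one coefficient. With about 212 analysed participants this is negligible. No new data, visits or change in sample size are needed.
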